
### Sample size calculation

The sample size calculation was performed to compare the improvement in disability (eg, changes in ODI scores) from baseline to 16 weeks between MC+ILEX and free-weight resistance training exercise groups. This calculation was conducted using PASS 2023 software for two-sample t-test based on effect size. The minimum required sample size is 90 (45 per group) to detect a standardised effect size of 0.60 (Cohen’s d effect size), with 80% statistical power at the significance level of 0.05 (two-sided test), assuming an equal variance within the low (LSIQ<9) and high (LSIQ≥9) instability strata.^21^ Cohen’s d effect size of 0.60 falls within the range considered as a medium effect.^100^ This effect size is a conservative choice for the sample size calculation, given that the estimated Cohen’s d is approximately 0.79 based on the disability improvement observed in the MC+ILEX group from our previous work^35^ (mean=9.7, SD=10) and the disability improvement reported by Welch *et al*^34^ for the free-weight resistance training exercise group (mean=17.5, SD=5). A total of 106 participants (53 per group) will be recruited to account for a 15% loss to follow-up.^35 101^

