### Statistical analysis

For the primary outcome, we will employ linear mixed-effects model for repeated measures over time using ODI as the dependent variable. The model will include effects for group (MC+ILEX vs free-weight resistance training), time (baseline vs 16 weeks) and group by time interaction. LSIQ score (high >9 and low ≤9) will be incorporated as a covariate and an unstructured covariance matrix will be used. Within the mixed model, we will calculate 95% CIs and p values for the two group contrasts, and for changes in ODI score within each group over 16 weeks. We will conduct similar analyses focusing on multifidus muscle composition and lumbar extensor muscle strength as separate dependent variables. To investigate if changes in multifidus muscle composition mediate improvements in disability, path analysis will be conducted to test the following paths: (a) group allocation at baseline (independent variable) → changes in multifidus muscle composition from baseline to 16 weeks (mediator); (b) changes in multifidus muscle composition from baseline to 16 weeks → changes in disability score (eg, ODI) from baseline to 16 weeks (dependent variable); and (c) group allocation at baseline → changes in disability score from baseline to 16 weeks. LSIQ score (high >9 and low ≤9) will be included in the model as an exogenous variable. For paths (b) and (c), disability score at baseline will be included as exogenous variables as well. The direct, indirect and total effects of treatment on the change in multifidus muscle composition and its 95% CI will be calculated based on non-parametric bootstrap. In addition, the mediation percentage is defined as the ratio of the indirect effect to the total effect, thereby quantifying the size of the mediation effect. The significance of the mediation effect will be tested using bootstrap sampling (times=1000). The model fit will be assessed using the following model fit indices: comparative fit index, Tucker-Lewis index and root mean square error of approximation.^102^ To explore if baseline score on the LSIQ can moderate the response to exercise training in chronic LBP at 16 weeks, we will conduct a linear regression model with changes in multifidus muscle composition from baseline to 16 weeks as the dependent variable. The independent variables will include group, LSIQ score (high >9 and low ≤9) and the interaction between group and LSIQ score (high >9 and low ≤9). Multifidus muscle composition at baseline will be adjusted as covariates in the model. Similar analyses will be conducted with changes in ODI score, multifidus size, lumbar extensor strength, pain, sleep and quality of life score from baseline to 16 weeks as the dependent variables, separately. Both complete case analysis and multiple imputation will be conducted to handle missing data. Any participant characteristics identified to be associated with missingness and the outcome will be integrated into the multiple imputation process. This will be accomplished using the fully conditional specification method fitted using predictive mean matching approach. Given the potential for missing data that are not missing at random, we will perform a sensitivity analysis to assess the robustness of our findings under the most unfavourable assumptions about the missing data. In this analysis, if we show that the MC+ILEX group is more effective than the free-weight resistance training exercise group in improving patients’ disability, all missing outcomes at 16 weeks will be imputed with the worst observed outcome in the MC+ILEX group and the best observed outcome in the free-weight resistance training exercise group, and vice versa.

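### At the planned effect and loss, the only analysis for data missing not at random removes significance almost every time, and it has no version for a null result

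*Protocol article*

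**What the plan says.** The Statistical analysis section of the protocol article plans complete-case analysis and MI (fully conditional specification with predictive mean matching) for missing data. It then adds one sensitivity analysis for data that may be missing not at random, openly described as a worst case.

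The condition is "if we show that the MC+ILEX group is more effective than the free-weight resistance training exercise group in improving patients’ disability". In that event "all missing outcomes at 16 weeks will be imputed with the worst observed outcome in the MC+ILEX group", and missing values in the free-weight arm take the best value observed there. A closing 'vice versa' mirrors the rule for a free-weight win. The section describes no intermediate departure from missing at random (MAR), and no version for a result in which neither arm is shown better.

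The Sample size calculation section supplies the scenario: d = 0.60 on change in ODI, 80% power, two-sided 0.05, 45 evaluable per group. It then states: "A total of 106 participants (53 per group) will be recruited to account for a 15% loss to follow-up".

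**The concern.** An MNAR sensitivity analysis should show how far the missing data must depart from MAR before the conclusion changes. This rule tests one point only, the most extreme, and gives every missing participant in an arm the value of that arm's single most extreme completer. At 15% loss the resulting shift could be as large as the effect the trial is built to detect. If so, the analysis fails whether or not dropout was informative.

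The trigger is a second gap. Non-random dropout can hide a difference as well as create one, and a null result is a real possibility when two active 16-week exercise programmes are compared. The article plans no MNAR analysis for that case.

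**Working it through.** **Inputs.** From Sample size calculation: d = 0.60, 45 evaluable and 53 randomised per arm, so 8 missing per arm (8/53 = 15.1%). Assumed, because the article does not give them: normal outcomes, equal SDs, equal loss by arm, and a baseline to week-16 correlation r of 0.4 to 0.7. Each arm's own extreme is used; extremes pooled over both arms would be at least as severe.

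**The plan's own figures.** The normal approximation gives 2 × (1.960 + 0.842)² / 0.60² = 43.6, so 44 per arm. The exact t-test gives 44.6, so 45, with power 80.4%. Allowing for loss, 90/0.85 = 105.9, so 106, and 45/0.85 = 52.9, so 53. The stated numbers reproduce.

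**Shift in the contrast.** After imputation an arm's mean moves by (8/53) × (extreme − mean). The expected extreme of 45 normal values is about 2.2 SD from the mean. The two arms move towards each other:

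shift = 2 × (8/53) × 2.2 × s = 0.66 × s

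Here s is the week-16 SD divided by the SD of change, which is 1/√(2(1 − r)) for equal SDs at both times.

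- r = 0.4: s = 0.91, shift 0.61 SD
- r = 0.5: s = 1.00, shift 0.66 SD
- r = 0.6: s = 1.12, shift 0.74 SD
- r = 0.7: s = 1.29, shift 0.86 SD

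All of these equal or exceed the planned 0.60.

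**Effect on the variance (s = 1).** Eight repeated extreme values raise each arm's variance to about 45/53 + (45 × 8/53²) × 2.2² = 0.85 + 0.62 = 1.47, an SD of 1.21. The smallest significant difference with 53 per arm becomes about 1.98 × √(2/53) × 1.21 = 0.47 SD. To survive, the observed effect must therefore be about 0.66 + 0.47 = 1.13 SD.

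**Simulation.** Values were missing completely at random, so the true effect was intact. With two time points and complete data, the group-by-time contrast is essentially a t-test on change. Results are among trials significant before imputation, at d = 0.60 with 8 missing per arm (3,000 trials per setting):

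| r | Still significant | Mean estimate (SD) | Sign reversed |
|---|---|---|---|
| 0.4 | 2.5% | 0.06 | 40% |
| 0.5 | 1.6% | 0.00 | 51% |
| 0.6 | 0.8% | −0.07 | 65% |
| 0.7 | 0.2% | −0.19 | 81% |

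A second set of 20,000 trials, imputing directly on the change scale, gave 80.5% significant at first. Of those, 1.7% stayed significant, the mean estimate was 0.01 SD and the sign reversed in 52%. Reversal that is itself significant is rare, 0 to about 1.5%.

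**Variants, as the share losing significance.**

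- Random 15% loss per arm: 96%. Correlation 0.3: 95%. Bounded ODI in 2-point steps (assumed baseline mean 30, SD 10): 98%.
- Larger effects with 8 missing per arm: d = 0.79, 91%; d = 1.0, 71%; d = 1.2, 39%. The article's own changes (9.7, SD 10, against 17.5, SD 5): 68%.
- Lower loss at d = 0.60: 1 missing per arm, 16%; 2, 37%; 4, 75%; 6, 93%.

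**A graded alternative.** The 8 missing values per arm were shifted against the winning arm and in favour of the other. Significance was kept in about 97%, 89%, 76%, 57% and 39% of significant trials at shifts of 0, 0.25, 0.5, 0.75 and 1.0 SD. This used one random draw per missing value, so full MI would give somewhat different percentages. What matters is that the answer is graded.

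**The case against.** The strongest reply is that the plan describes the analysis for what it is. A declared worst case is meant to be hard to pass, and severity alone is no error. The primary inference comes from the mixed model, and the bound changes neither its estimate nor its p value. It errs in the conservative direction. The 15% is a recruitment allowance, and since the ODI can be completed by app, phone or paper, actual loss may be lower. Details of MNAR modelling are also often left to a statistical analysis plan, which is not shown.

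Much of this stands, and it rules out several stronger readings:

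- A reader might infer that the rule can never show robustness. It can be survived with only a few per cent missing or an effect well above 1 SD, and survival would then be strong evidence.
- A reader might infer that a sound positive trial must be reported as not robust. The article has no rule under which failing the bound changes the conclusion.
- A reader might infer that a null result gets no sensitivity analysis at all. Complete-case analysis and MI are planned whatever the result; only the MNAR part is absent.
- A reader might infer that the rule applies only to an MC+ILEX win. It is symmetric.

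The reply does not remove the core of the point. The article itself fixes this rule and its trigger, gives it the task of assessing robustness, and names nothing between MAR and the extreme. Even at half the planned loss, 75% of true positives lose significance.

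**Conclusion.** The concern holds in a limited form. At the planned effect and loss, the rule removes significance in about 97% to 99.8% of truly positive trials although the missingness is harmless. In that scenario a failure cannot separate a robust result from a fragile one. A null result has no MNAR analysis.

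The range rests on normal outcomes, equal SDs, 8 missing in each arm and a correlation of 0.4 to 0.7. Random loss or a correlation of 0.3 lowers it only to about 95% or 96%. It depends strongly on actual loss and on the true effect. Losing significance should not be read as showing that the other arm is better.

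The primary analysis is unaffected. The change should be made because the sponsor would otherwise have to report a near-certain failure, or explain away its own prespecified analysis after seeing the data.

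**What to change.** Make the main MNAR analysis a delta-adjusted MI tipping-point analysis:

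1. Impute 16-week ODI by arm under MAR, using the MI already planned.
2. Shift the imputed values over a grid of deltas in ODI points, applied separately to each arm, so that unequal departures are covered.
3. Re-analyse with the primary model, combine by Rubin's rules, and report the deltas at which the conclusion changes. State in advance which deltas the team regards as plausible.
4. Run it whatever the primary result. After a null result, report the deltas at which a difference would appear.
5. Keep the worst/best-observed-value case only as a labelled outer bound, and say that failing it is expected at around 15% loss.

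If the statistical analysis plan already contains such an analysis, it is enough to bring the protocol wording into line with it.

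The cost is a little more programming on the planned MI. No new data, visits or participants are needed.

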
### Data integrity

Data will be collected directly through the *ManagingLife* application. All data will be reviewed for completeness, and any inconsistencies will be investigated and corrected as needed. Deidentified data will be stored on a secure institutional managed server that complies with privacy standards. Access to the password-protected database will be restricted to authorised members of the study personnel.

### Retention of documents

Investigators will maintain complete and accurate research records to ensure full documentation of the study procedures and to support verification of study data. In accordance with institutional and federal research data retention requirements, all study data will be securely archived by Concordia University for a minimum period of 7 years.

### Patient and public involvement

The study protocol was developed in collaboration with clinicians and scientists with extensive experience in treating individuals with LBP. Patients with lived experience were also involved in the development of this study.

## Ethics and dissemination

### Ethics approval and trial registration

This study received ethics approval from the Central Ethics Research Committee of the Quebec Minister of Health and Social Services (CCER-25-26-14). The trial was registered prospectively (ISRCTN14864451) on ISRCTN study registry. Any important protocol modifications (eg, changes to eligibility criteria, outcomes or study procedures) will be submitted to the Research Ethics Board as a formal amendment prior to implementation. All coinvestigators and relevant study personnel will be notified of approved changes.

### Dissemination of findings

The principal investigator will present or publicise the results of this project in peer-reviewed journal publications and at national/international related conferences or meetings. The subject’s personal information will never be linked to any of the scientific data in question. On completion of the trial, and after publication of the manuscripts, data requests can be submitted to the primary investigator (MF).

### Timeline and feasibility

This project is expected to begin in winter 2026 and data collection should be completed within 2 years. We conducted a pilot trial at the School of Health (Concordia University) and were able to recruit our required sample of 50 participants within 4 months (eg, we had two recruitment periods of 2 months each). This was during the COVID-19 pandemic (2020–2021) while we had many additional hurdles and procedures in place. We expect to recruit 10 participants per month, which is in line with our pilot studies.^25 35 103^ We will recruit half of the required sample (53 patients) in the first year and the second half of the sample during the second year.

### Steering committee

The steering committee will consist of the principal investigator and coinvestigators, including two designated knowledge users. The committee will convene twice annually to review the study progress and provide oversight on study procedures. A data safety and monitoring committee will not be established, as adverse events are not a factor of concern in this trial.

## Discussion

This innovative and comprehensive RCT is designed to address multiple long-standing gaps in the exercise-based management of chronic LBP, offering a multifaceted approach that integrates clinical precision, mechanistic insight and patient-centred care. We will adopt a targeted care strategy by integrating the PDDM and LSIQ to screen and include a homogeneous sample of patients (eg, primary nociceptive pain) who are most likely to benefit from the exercise interventions, thereby advancing precision rehabilitation. This trial will also investigate whether improvements in muscle morphology mediate changes in disability, using state-of-the-art imaging and standardised measures of muscle composition. By linking therapeutic outcomes to underlying mechanisms, this study aims to inform and enhance clinical decision-making. Furthermore, the trial is designed to apply optimal exercise dose prescriptions based on previous evidence to produce meaningful improvements in paraspinal muscle quality and function.^34 35 53 104^ In addition to the exercise interventions, strategies will be implemented to enhance therapist confidence, foster effective communication, deliver consistent positive messaging and build a strong therapeutic alliance. Finally, a qualitative inquiry will be conducted to capture the depth and nuance of patient perspectives and satisfaction before and after the intervention, providing a comprehensive understanding of the patient experience and further informing clinical practice.

A limitation of this protocol is the lack of blinding for the therapists delivering and the participants undergoing MC+ILEX and free-weight resistance training due to the nature of the exercise interventions. However, this is a common and often unavoidable limitation of exercise-based interventions. Another limitation is that this trial will be conducted at a single research centre, which may affect the generalisability of the findings.

This trial will provide a unique opportunity to evaluate the effectiveness of MC+ILEX as compared with free-weight resistance training in a homogeneous sample of participants with primary nociceptive chronic LBP. The findings will provide robust scientific evidence to support a targeted LBP intervention. These results will have important implications for clinical practice, offering cost-effective and personalised treatment strategies. Furthermore, the study will contribute to the advancement of knowledge in musculoskeletal rehabilitation and inform future research directions in the field.
